**Figure 3 F3:**
[figure not shown]
Genetic dashboard included in the District Health Information System V.2-based Integrated Malaria Information Storage System (iMISS) to facilitate data accessibility and use. The iMISS, which is currently being rolled out, includes case data, focus investigations, entomological surveillance data and intervention data. A genetic dashboard has already been created into IMISS corresponding to antimalarial resistance and *pfhrp2/3* deletion profiles, developed in collaboration with National Malaria Control Programme. Specific dashboards for genetic connectivity and case classification in very low-transmission areas (estimated proportion of imported cases, together with travel history and other parameters obtained from case-based notification tools) will be also considered. CNV, copy-number variant; RDT, rapid diagnostic test; SP, sulfadoxine–pyrimethamine.

### Study outcomes and analysis plan

This project has six primary endpoints. First, prevalence of drug-resistance markers at individual codons, or multicodon haplotypes if successfully phased, will be calculated at provincial level as the number of samples carrying a mutant allele or haplotype out of all samples with a valid genotype for the respective locus. Differences in the prevalence of drug resistance markers (1) between provinces; (2) between years and (3) after interventions will be evaluated using Fisher’s exact test. If emerging VOCs are identified, genetic relatedness between infections will be assessed to describe potential sources and origins of the variants. Allele frequencies will be estimated using methods that account for sample polyclonality.^45^

Second, the prevalence of suspected false-negative HRP2-RDT results among symptomatic patients with *P. falciparum* malaria will be determined at the regional level using the DRpower tool, which accounts for intracluster correlation when estimating the prevalence.^32^ The prevalence of false-negative HRP2-RDT caused by *pfhrp2/3* deletions will be determined as the number of *pfhrp2* or *pfhrp3* deletions confirmed by qPCR^40^ divided by the total number of confirmed cases in a given region.

Third, sources of importation and transmission will be identified using genetic relatedness (identity-by-descent [IBD]) between pairs of samples estimated using Dcifer software.^46^ The fraction of highly related pairs (using a threshold in IBD) will be calculated for samples within each province and between different provinces to characterise the spatial connectivity of parasite genetic populations. Isolation-by-distance will be calculated to assess the extent to which genetic relatedness decreases with geographic distance. Cases from areas targeted for elimination will be classified as local or imported infections by combining data on participants’ reported travel (dates and duration of travel), epidemiologic data from source and destination areas (malaria incidence estimated from DHIS2 data) and genetic data from source and destination areas (relatedness of samples via IBD). Outbreaks will be detected in the study areas using EpiFRIenDs software,^20^ and genetic relatedness analysis within outbreaks will be performed to quantify the number of transmission events causing the outbreak.

Fourth, genetic diversity metrics will be assessed to characterise natural and intervention-driven changes in transmission.^13^,^1647 48^ Correlation analysis will be used to test the relationship between parasite genetic diversity metrics (locus-based expected heterozygosity), within-host diversity data (multiplicity of infection [MOI] and effective MOI,^45^ Wright’s inbreeding coefficient, the proportion of polyclonal infections), the proportion of highly related samples based on IBD), RDT positivity rates at ANC clinics and DHIS2-based malaria incidence, the latter corrected for several potential biases (health-seeking behaviour, reporting and testing and alternative causes of fever).^1^ The use of microhaplotype-based genetic diversity markers to discriminate recrudescence from new infections in TESs will be compared with the currently recommended WHO/MMV *msp1*/*msp2*/*polyA*.^49^ In addition, the genetic diversity in the C-terminal region of the circumsporozoite protein that encompasses T-cell epitopes included in the R21/Matrix-M^23^ and RTS,S^28^ malaria vaccines will be determined by comparing the sequence reads with those in the *P. falciparum* 3D7 reference genome.

Finally, *P. falciparum* parasite rates and genomic indicators will be generated for the first ANC visit. RDT positivity rates and Insecticide-treated nets/indoor residual spraying coverage data will be compared with unbiased gold standard household-level data collected through the Malaria Indicator Survey. Time series analysis and logistic multivariate regression will be considered to assess seasonality and to estimate the change in parasite rates after introduction of antimalarial interventions, including an interaction term, area#timepoint, to identify effect differences among interventions introduced in the country (chemoprevention, malaria vaccine, vector control). A mechanistic transmission model, malariasimulation (https://mrc-ide.github.io/malariasimulation/), will be fitted to monthly ANC prevalence, adjusted for gravidity, using the siftr R package developed by Imperial College London to generate estimates of transmission and potential clinical case burden. Rates of polymorphisms associated with antimalarial, diagnostic and vaccine resistance will be compared in parasites collected from pregnant women and the general community.

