## Methods and analysis

### Study design and sample size calculations

This is a prospective genomic surveillance study of *P. falciparum* samples to be collected between 2024 and 2026 from a variety of transmission intensities and geographies in Mozambique. Sampling design and efforts will be driven by target use cases. A multicluster probabilistic health facility sampling (HFS) sampling scheme^31^ will be followed to detect *pfhrp2/3* deletions and markers of antimalarial resistance across the 10 country provinces (figure 2A). Dried blood spots will be collected from a consecutive sampling of 60 RDT-confirmed malaria clinical cases per health facility, from a systematic random sample of four health facilities per province (figure 2B and table 1). Using the DRpower tool and associated web-based *pfhrp2/3* Planner,^32^ the study power was estimated to detect the prevalence of *hrp2/3* deletions above the 5% threshold at the regional level.^33^ Assuming an intracluster correlation coefficient (ICC) of 0.05 based on historical data (https://mrc-ide.github.io/DRpower/articles/historical_analysis.html), power was estimated at 92.4% (91.9%–92.9%) in regions with three provinces (12 clusters of 60 samples) and 96.9% (96.5–97.2%) in regions with four provinces (16 clusters of 60 samples). Power remains high under the more pessimistic assumption of ICC=0.1, being 78.6% (77.8%–79.4%) and 86.3% (85.6%–87%) for regions with 3 and 4 provinces, respectively. This same design will be used to estimate the prevalence of *pfdhps* mutations at codon 540 at the province level (margin of error analysis). Assuming a mutation prevalence of 90%,^34^ prevalence will be estimated to within 4.8% margin of error for ICC=0.01 and within 7.5% margin of error for ICC 0.05^31^ (assuming lower ICC than for *pfhrp2/3* given the lower variance between clusters expected when looking at smaller geographic scale). Finally, the design will be used to detect the presence of variants of concern (VOCs), namely *pfkelch13* markers of artemisinin partial resistance and *pfdhps-*581 marker of SP resistance, at the province level (presence/absence analysis). Assuming VOCs at 1% prevalence in the population, the design has 85% power to detect VOCs if ICC=0.01 and 67% if ICC=0.05^31^.

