### Enrolment of participants

HFSs will be conducted during the first trimester of 2025. Children aged 2–10 years with fever or history of fever (table 3) will be screened using routine HRP2-based RDTs (First Response Malaria Antigen *P. falciparum* HRP2 [Premier Medical] or SD Bioline Malaria Ag Pf, 05FK50 [Abbott,] depending on national procurement at the time of the study) and an additional confirmatory RDT targeting *P. falciparum* LDH (Biocredit Malaria AG Pf (pLDH) C14RHG25, Rapigen) selected from the recommended options in the WHO master protocol.^33^ Assuming that 85% of samples will be of high sequencing quality, the sample size per health facility will be increased from 60 to 71. Dried blood spots will be collected from study participants if either test is positive, and samples with discrepant RDT results will be used to detect *pfhrp2/3* deletions. The number of people to be screened at each health facility and the duration of recruitment to achieve the sample size will depend on the RDT positivity rate among study participants meeting the eligibility criteria.

**Table 3 T3:** Study eligibility criteria

Inclusion criteria	Exclusion criteria
Children aged 2–10 years of age (cluster sampling). >6 months of age (dense sampling).	Any symptoms of severe malaria.
Fever (axillary temperature≥37.5°C) or history of fever in the preceding 24 hours.	
At least one positive parasitological test for malaria diagnosis via RDT*.	Negative parasitological test for malaria via RDT (except any women at their first ANC visit, who will be recruited before testing for malaria with an RDT).
OR	
Pregnant women (≥12 years of age) attending first antenatal care visit.	Unwilling to provide informed, written consent.
AND	
Informed, written consent to participate from participant and/or guardian.	History of antimalarial treatment in the last 14 days

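### Fisher's exact test for resistance-marker differences ignores the facility clustering the plan assumes; between-province false positives for common markers are about 9–10% (ICC 0.01) to 29% (ICC 0.05)

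*Protocol article*

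**What the plan says.** Under 'Study outcomes and analysis plan', the first primary endpoint is a provincial prevalence: samples carrying the mutant allele or haplotype, divided by all samples with a valid genotype. Differences "1) between provinces; (2) between years and (3) after interventions will be evaluated using Fisher’s exact test". No allowance for facility or clinic is stated. The one further adjustment named for this endpoint concerns polyclonal infections.

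Under 'Study design and sample size calculations', the health facility survey takes a "consecutive sampling of 60 RDT-confirmed malaria clinical cases per health facility", "from a systematic random sample of four health facilities per province". For the *pfdhps* 540 mutation, at an assumed prevalence of 90%, "prevalence will be estimated to within 4.8% margin of error for ICC=0.01 and within 7.5% margin of error for ICC 0.05". The Discussion treats these as the typical and the pessimistic case.

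The second primary endpoint, false-negative HRP2-RDT results, is to be estimated with a tool "which accounts for intracluster correlation when estimating the prevalence". That provision is not extended to the resistance markers.

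**The concern.** Children attending one facility share local transmission and local parasite lineages, so their genotypes resemble one another more than those of children from different facilities. The plan accepts this when it sets the sample size and when it analyses its second endpoint. The only test named for the first endpoint assumes it away.

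When samples are clustered, a pooled provincial proportion varies more than a binomial proportion does. Fisher's test then reads ordinary facility-to-facility variation as a difference between provinces. Resistance profiles are meant for a national dashboard and for decisions of the control programme, so a false difference would suggest a geography of resistance that is not there.

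**Working it through.** **Inputs from the article.** Four facilities per province; 60 valid samples per facility ("Assuming that 85% of samples will be of high sequencing quality", 71 are collected, since 60/0.85 = 70.6), hence 240 per province; prevalence 0.90 for *pfdhps* 540 and 0.01 for variants of concern; ICC 0.01 and 0.05. **Assumption:** two-sided level 0.05, since the article gives none.

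**1. Reproduce the plan's own figures.** Design effect = 1 + (60 − 1) × ICC, which is 1.59 at ICC 0.01 and 3.95 at ICC 0.05.
- Margin = 1.96 × √(0.90 × 0.10 × design effect / 240) = 4.79 and 7.54 percentage points, against the stated 4.8% and 7.5%.
- Power to find a 1% variant = 1 − [beta-binomial P(0 of 60)]⁴ = 84.9% and 66.8%, against the stated 85% and 67%.

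So the clustering model used below is the plan's own.

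**2. Large-sample expectation.** For two provinces with equal prevalence, the unadjusted test statistic has standard deviation √(design effect) instead of 1. The rejection rate is 2 × [1 − Φ(1.96/√design effect)] = 12.0% at ICC 0.01 and 32.4% at ICC 0.05. Fisher's test is conservative, so its actual rates should be somewhat lower.

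**3. Simulation of Fisher's test, two provinces, no true difference.** Facility prevalences are drawn from a beta distribution with parameters p(1 − ICC)/ICC and (1 − p)(1 − ICC)/ICC, then 60 binomial samples per facility; 20,000 replicates.

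| True prevalence | ICC 0 | ICC 0.01 | ICC 0.05 |
|---|---|---|---|
| 90% | 3.3% | 9.4% | 29.1% |
| 50% | 3.9% | 10.5% | 30.7% |
| 5% | 2.9% | 8.7% | 26.5% |
| 1% | 0.7% | 2.9% | 13.4% |

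Repeat runs at 90% prevalence gave 9.2% to 9.8% and 28.6% to 29.4%. If the ten provinces are instead compared in one overall test (chi-square approximation, 90% prevalence), the rates are 31% and 89%.

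**4. Same sites, two periods.** Here the result depends on the correlation of a site's true prevalence between periods. The article gives no such figure, so the whole range is shown (90% prevalence, Gaussian copula). For antenatal clinics, 2870 positives a year over ten provinces is 287 per province, taken as two clinics of about 143. The article gives no ICC for clinics, so the facility values are assumed.

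| Sites | ICC | Corr. 0 | 0.5 | 0.8 | 1 |
|---|---|---|---|---|---|
| Four facilities × 60 | 0.01 | 9.4% | 6.5% | 4.5% | 3.5% |
| Four facilities × 60 | 0.05 | 28.7% | 18.1% | 9.5% | 3.1% |
| Two clinics × 143 | 0.01 | 17.9% | 11.0% | 6.5% | 3.5% |
| Two clinics × 143 | 0.05 | 45.8% | 32.8% | 17.5% | 3.3% |

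**5. Do cluster-aware tests restore the level?** Between two provinces at 90% prevalence, at ICC 0.01 and 0.05 respectively: a z test adjusted by the design effect rejects 4.9% and 4.3%; a t test on the four facility proportions per province, 5.1% and 4.3%. A quasi-binomial test with dispersion pooled over 40 facilities rejected between 4.3% and 6.1% across runs.

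**The case against.** The strongest defence is that the endpoint itself is an estimated prevalence, which near-equal clusters leave unbiased. The precision the article quotes already includes the design effect, and no stated decision rule hangs on a Fisher p-value. That stands, and it limits the harm to the comparisons. It does not excuse the test: the article names it outright, and it contradicts the article's own design assumptions, so this is not a detail left to an analysis plan.

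A reader might infer more than the article supports:
- **That all three comparisons will reject far above 5%.** The facility survey has one round, in the first quarter of 2025. Most antenatal clinics in Table 1 are sampled throughout 2024 and 2025, so comparing years there sets the same sites against themselves. Site effects then partly or wholly cancel, and with full persistence the rate is about 3%. For these comparisons the right word is 'may'.
- **That every marker is affected.** At 1% prevalence and ICC 0.01 the rate is below 5%.
- **That error rates above 40% apply to the facility survey.** At 90% prevalence this needs ICC 0.10, which the article uses only for *pfhrp2/3* at regional level; it expressly assumes less clustering for *pfdhps* within provinces.
- **That reported intervals will be too narrow.** An unadjusted margin would be 1.96 × √(0.09/240) = 3.8 points, but the article specifies no interval method.
- **That 45 pairwise tests will be run without correction.** The article does not say the comparisons are pairwise, and multiplicity is commonly left to the analysis plan.

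**Conclusion.** The point holds for between-province comparisons of common markers. Under the plan's own ICCs, a nominal 5% Fisher test with 4 × 60 samples per province rejects about 9–10% of the time in the typical case and about 29% in the pessimistic case at 90% prevalence. The result is much the same at 50% and slightly lower at 5%. For a 1% marker it is about 3% and 13%. Between-year and post-intervention comparisons may be inflated too. The size cannot be fixed from the article, because it turns on which sites are compared and how stable they are.

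These figures assume a two-sided 0.05 level, beta-binomial clustering and equal facility sizes. For the antenatal clinics they also assume that the facility ICCs carry over. The named test should be replaced; the sampling design and the prevalence estimates need no change on this account.

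**What to change.** Replace Fisher's exact test by a comparison that respects the clusters, with the details set by the contrast.

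- **Between provinces, facility survey.** Use a quasi-binomial, beta-binomial or mixed logistic model with province as a fixed effect and facility as the cluster. Pool the dispersion over all 40 facilities (40 − 10 = 30 df), since four per province are too few to estimate it separately. Report provincial prevalences with intervals from the same model.
- **Between years or before and after an intervention.** Compare within sites and include a site-by-period variance or overdispersion term. A site intercept alone misses the year-to-year variation within a site, which is what inflates these tests.
- **Antenatal clinics.** The 30 df do not carry over: Table 1 lists 20 clinics, with only one in Nampula. Where a province has a single clinic, take the dispersion from the pooled clinics and do not attribute a clinic difference to the province.

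The significance level should be stated at the same time. The cost is analysis wording and a few lines of code. Some differences will become less significant. No new data are needed.

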**Trial registration number:**

NCT06529237.

STRENGTHS AND LIMITATIONS OF THIS STUDYA multicluster probabilistic health facility sampling scheme will be used to detect *pfhrp2/3* deletions and markers of antimalarial drug resistance across the 10 provinces in Mozambique.High-throughput sequencing will be used to target 165 microhaplotypes informative about *P. falciparum* genomic diversity and relatedness as well as markers associated with antimalarial drug resistance, diagnostic failure and vaccine targets.A new outbreak detector (EpiFRIenDs) will be used for outbreak monitoring and investigation of transmission sources in malaria elimination areas.Malaria incidence will be calculated considering potential biases (health-seeking behaviour, reporting and testing and alternative causes of fever) and used to compare its relationship with metrics of parasite genetic diversity.District Health Information System V.2-based genetic dashboard will be used for an easy visualisation of genomic outcomes.

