### Molecular analyses

We will genotype samples using targeted amplicon sequencing to characterise sequence (single-nucleotide polymorphisms [SNP], microhaplotypes and haplotypes) and copy number (duplications and deletions) variants. We will use the MAD^4^HatTeR targeted sequencing panels (developed at EPPIcenter—UCSF and Paragon Genomics, California, USA) on approximately 7690 *P*. *falciparum* samples (based on expected positivity rates). MAD^4^HatTeR is a modular assay that targets up to 239 *P*. *falciparum* amplicons of ≈250 bp, which include microhaplotypes informative about genomic diversity and relatedness in Africa,^19 35^ targets for *pfhrp2/3* deletions,^6 7^
*pfcsp* polymorphisms encompassing the TH2R and TH3R epitopes included in the R21/Matrix-M^23^ and RTS,S vaccine^28^ and drug resistance markers in 13 genes,^34^ including polymorphisms associated with resistance to artemisinin (*pfkelch13*),^36^ SP (*pfdhfr* and *pfdhps*),^37^ chloroquine (*pfcrt*^38^) and amodiaquine (*pfcrt* and *pfmdr1*). Additionally, targets for four non-*falciparum* species detection are included. Targeted amplicons obtained by PCR on genomic DNA using Illumina-specific adaptors and sample-specific barcode will be pooled to create a single product library, which will be sequenced (paired end 150 bp) on a MiSeq Illumina sequencer at CISM or higher performance equipment when available. We will use qPCR to determine parasite density,^39^ confirm *pfhrp2/3* deletions,^40^
*Plasmodium* species^41 42^ and copy-number variants (CNVs) in markers of piperaquine and mefloquine resistance (*pfpm2* and *pfmdr1*).^43^ We will also perform whole-genome sequence a subset of *P. falciparum* samples to generate a longitudinal catalogue of generate a longitudinal catalogue of genome-wide variations.

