This project, guided by programmatic priorities and based on collaborative efforts, aims to promote the use of MMS indicators for decision-making. Data will be shared with the NMCP through biannual meetings and workshops to train in the interpretation of genomic data. A brochure in Portuguese will be produced every 4 months to present the main results of the project and shared with stakeholders in the surveillance field (figure 4; online supplemental appendix 1). Genetic data will be included in the DHIS2-based iMISS (figure 3) to facilitate data accessibility and use. The project will also support clinical trials in producing key outcomes (PCR-corrected efficacy in therapeutic efficacy trials) and in assessing the impact of interventions on the development of malaria resistance (PMC, SMC and MDA). Finally, the project will contribute to a curated sequence catalogue of targeted and whole-genome sequences that started with samples collected in 2015, which will be used for studying the evolution of *P. falciparum* parasites in response to changing national malaria control and elimination policies.

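### Low relatedness between infections cannot tell whether an emerging resistance variant has one origin or several; compare the haplotypes around the resistance locus among carriers

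*Protocol article*

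**What the plan says.** Under the first primary endpoint (Study outcomes and analysis plan), the step that follows detection of an emerging variant of concern is that "genetic relatedness between infections will be assessed to describe potential sources and origins of the variants". Nothing in that sentence refers to the resistance locus itself.

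The article defines relatedness once, under the third endpoint: "genetic relatedness (identity-by-descent [IBD]) between pairs of samples estimated using Dcifer software". The summary there is "The fraction of highly related pairs (using a threshold in IBD"), with no threshold value given. The loci behind it are described in the strengths and limitations list ("High-throughput sequencing will be used to target 165 microhaplotypes") and in Molecular analyses ("microhaplotypes informative about genomic diversity and relatedness in Africa").

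Three related provisions are not tied to the origin question:
- The adjustment for polyclonality next to the quoted sentence concerns allele frequencies. Phasing concerns codons within a marker haplotype, and only where it succeeds.
- Molecular analyses says "We will also perform whole-genome sequence a subset of" the samples, to build a longitudinal catalogue. Carriers of a variant are not named as candidates.
- The Discussion describes a "curated sequence catalogue of targeted and whole-genome sequences that started with samples collected in 2015", intended for studying parasite evolution.

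**The concern.** A statement about where a variant came from concerns the lineage of one locus. Relatedness between infections concerns the average ancestry of whole samples. The two come apart in two ways.

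First, each outcross replaces about half of the unlinked genome, while the stretch next to the variant is broken only by nearby crossovers. Carriers descended from one ancestor can therefore look unrelated across the genome and still share the haplotype around the variant.

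Second, in an infection with several strains, a sample-level IBD value does not say which strains are related. They need not be the ones carrying the variant.

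At stake is the interpretation of a pfkelch13 or pfdhps-581 finding. High relatedness would be informative. Low relatedness would leave open whether one variant is spreading or several have arisen, and the named method contains nothing to resolve that.

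**Working it through.** **The plan's own figure.** The article gives no operating characteristic for the origin analysis. The nearest is detection power, "Assuming VOCs at 1% prevalence in the population": 85% at ICC 0.01 and 67% at ICC 0.05, per province. With 4 facilities × 60 cases and a beta-binomial model, power = 1 − [B(a, b+60)/B(a, b)]^4, where a = p(1/ICC − 1), b = (1 − p)(1/ICC − 1) and p = 0.01.
- ICC 0.01: a = 0.99, b = 98.01, giving 84.9%.
- ICC 0.05: a = 0.19, b = 18.81, giving 66.8%.

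Both stated figures are reproduced. The point below does not touch them.

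**Decay of genome-wide relatedness.** Let two carriers of one single-origin variant each be g outcrossed generations from their common carrier ancestor. At an unlinked locus both keep the ancestral allele with probability (1/2)^g × (1/2)^g = 4^−g: 0.25, 0.063, 0.016 and 0.004 for g = 1 to 4. This ignores loci linked to the variant, so it understates the genome-wide mean. A simulation that conditions on both parasites carrying the variant corrects for this. Its layout is assumed: 14 chromosomes, 15 Morgans, 168 evenly spaced loci, 1,500 pairs. The cut-offs are also assumed, because the article gives none.

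| g | 4^−g | simulated mean IBD | share ≥ 0.125 | share ≥ 0.25 |
|---|---|---|---|---|
| 1 | 0.25 | 0.28 | 98.5% | 63% |
| 2 | 0.063 | 0.09 | 19% | 0.4% |
| 3 | 0.016 | 0.04 | 0.2% | 0% |
| 4 | 0.004 | 0.02 | 0% | 0% |

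**What remains around the variant.** With 2g meioses separating the two carriers, the expected shared flank is 1/(2g) Morgans per side, or 100/g cM in total, ignoring chromosome ends. At g = 3 this is 16.7 cM per side, 33 cM in total. On the assumed layout, 33.3/1500 × 168 ≈ 3.7 panel loci fall in that segment. The simulation agrees. At g = 3 the 156 loci on other chromosomes contribute (156/168) × 0.0156 ≈ 0.0145. The remaining 0.036 − 0.0145 ≈ 0.0215 equals about 3.6 loci on the variant's own chromosome. Most of the surviving signal is thus near the variant, where a genome-wide average dilutes it.

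**Selfing.** If only a share t of transmission cycles is outcrossed, expected IBD at unlinked loci after k cycles per lineage is (1 − t/2)^(2k). It falls to 0.25 after about 1.0, 2.4, 5.2 and 13.5 cycles for t = 1, 0.5, 0.25 and 0.1. The article gives no value for t.

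**Which strain is related.** Suppose each infection has m strains, the carrier pair is related with probability r1 and any other pair with probability r0. The carrier pair's share of expected related pairs is r1/(r1 + (m² − 1)r0). All of these rates are assumptions.

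| r1, r0 | m = 2 | m = 3 |
|---|---|---|
| equal | 25% | 11% |
| 0.05, 0.01 | 63% | 38% |
| 0.5, 0.01 | 94% | 86% |

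The range is too wide to give a size for this part.

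**Number of carriers.** At 1%: 240 × 0.01 = 2.4 per province; 2,400 × 0.01 = 24 in the survey if every province were at 1%; 7,690 × 0.01 ≈ 77 per variant across all samples planned for amplicon sequencing.

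**The case against.** The sentence is short, conditional and descriptive. It does not say genome-wide, Dcifer or thresholded; those terms belong to the third endpoint, and applying them here is a reading. Comparing haplotypes around a locus is also, in a loose sense, an assessment of relatedness. Whole-genome sequencing, the catalogue, phasing tools and multiplicity-of-infection estimates are all planned, and a condensed article may leave their use to the full protocol.

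Much of this stands. The point is not that something was left out. The article names the evidence it will use on origin, defines only one relatedness measure, and low values of that measure do not answer the question.

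A reader might infer more: that the plan will declare separate emergences when carriers look unrelated, that it is biased in that direction, or that the error will be largest in the north. The documents do not support this. No rule equates low relatedness with independent emergence, and no count or classification of origins is planned. The article gives a north–south gradient in burden but no outcrossing, selfing or multiplicity figure. Nor does it say that a programme decision turns on one origin versus several. The 25% and 11% in the equal-rates row should not be taken as typical either: infections chosen because they share a rare variant are likely to be enriched for related carrier strains.

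**Conclusion.** The concern holds as a limit on what the named evidence can show. High relatedness between carriers, especially in monoclonal infections, supports recent shared spread. Low relatedness is compatible with one origin or several. Under full outcrossing to unrelated strains, that ambiguity sets in after about two to three generations per lineage (mean IBD 0.09, then 0.04); where selfing is common it takes longer. The size rests on the assumed genome layout and outcrossing rate. The direction of the argument does not. The polyclonality part holds in principle, but its frequency cannot be derived from the article.

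No endpoint estimate, sample size or power figure is affected. This is an inexpensive improvement in method.

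**What to change.** Add to the first endpoint that, when a variant of concern is found:
1. its carriers have priority in the planned whole-genome subset, monoclonal or variant-dominant infections first;
2. haplotypes flanking pfkelch13 or pfdhps are compared among carriers and against available wild-type and catalogue sequences;
3. statements on origin rest on these flanking haplotypes, and relatedness between infections is reported as evidence of recent spread;
4. the report states that low relatedness between infections does not exclude a shared origin.

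Cost: one extra comparison and a reallocation of whole-genome slots. At 1% prevalence that is about 24 survey carriers, or up to about 77 per variant if all roughly 7,690 samples are considered, plus any wild-type comparators not already sequenced. The article does not give the size of the whole-genome subset, so a ranking rule is needed in case carriers exceed the slots. Some low-density carriers will not yield usable data; for these the origin should be reported as undetermined.
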